### Safety reporting

This study has been approved by the ethics committee (METC) of the Academic Medical Centre Amsterdam and by the boards of management of all participating hospitals.

In accordance with the National Medical Research Act (WMO, Section 10, Subsection 1), the investigator will inform the subjects and the reviewing accredited METC in case it appears that the disadvantages of participation may be significantly greater than was foreseen in the research proposal. All observed or volunteered adverse events, regardless of suspected causal relationship to the intervention, will be recorded.

An adverse event (AE) is defined as an event after which the intervention has to be stopped. Reasons for discontinuation are placental abruption, cord prolapse, chorioamnionitis, fetal loss, fetal trauma due to puncture, premature labour and delivery.

A serious adverse event (SAE) is defined as fetal or maternal death or illness necessitating IC or CCU treatment. All SAEs will be reported to the accredited METC that approved the protocol, according to the requirements of that METC. In addition to the expedited reporting of SAE’s, the principal investigator will submit, once a year throughout the clinical trial, a safety report to the accredited METC.

A Data Safety Monitoring Board (DSMB) will be established prior to start of the trial.

### Sample size calculation

A sample size calculation was based on an expected rate of perinatal mortality of 70% with expectant management, to be reduced to 35% with amnioinfusion. Using a two-sided test, with a β-error of 0.20 and an α-error of 0.05 a sample size of 56 women (28 in each arm) is needed.

An interim analysis is planned after the follow up data of the first 28 women that have been included. The analysis will be performed using the O’Brien-Flemming alpha spending function meaning a nominal P value of less than 0.005 will be considered to indicate statistical significance [16]. If there is a significant difference in the primary outcome the trial will be stopped.

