**Methods/Design:**

Women with PPROM and persisting oligohydramnios between 16 and 24 weeks gestational age will be asked to participate in a multi-centre randomised controlled trial. Intervention: random allocation to (repeated) abdominal amnioinfusion (intervention) or expectant management (control). The primary outcome is perinatal mortality. Secondary outcomes are lethal pulmonary hypoplasia, non-lethal pulmonary hypoplasia, survival till discharge from NICU, neonatal mortality, chronic lung disease (CLD), number of days ventilatory support, necrotizing enterocolitis (NEC), periventricular leucomalacia (PVL) more than grade I, severe intraventricular hemorrhage (IVH) more than grade II, proven neonatal sepsis, gestational age at delivery, time to delivery, indication for delivery, successful amnioinfusion, placental abruption, cord prolapse, chorioamnionitis, fetal trauma due to puncture. The study will be evaluated according to intention to treat. To show a decrease in perinatal mortality from 70% to 35%, we need to randomise two groups of 28 women (two sided test, β-error 0.2 and α-error 0.05).

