### Statistical analysis

The analysis of the randomised clinical trial will be performed on an intention-to-treat principle. The differences between the amnioinfusion and expectant management will be assessed by calculating the ratio of the outcome rates in the two groups. Hence, the measure of association is a relative risk (RR) with a 95% confidence interval (CI), calculated using a log-binomial model. Time to delivery will be evaluated by Cox proportional hazard analysis, Kaplan-Meier estimates and tested with a log rank test.

In case of equivalence between outcomes, the analysis will be repeated on an “as-treated” basis. Subsequently, primary and secondary outcomes will be described in a subgroup of women with successful amnioinfusion (retention of infused fluid first 48 hours). All analyses will be adjusted for the fact that an interim analysis will be performed using the O’Brien-Flemming alpha spending function [18]. Consequently, a nominal P value of less than 0.049 will be considered to indicate statistical significance.

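### With 28 women per arm, exact power of the planned relative-risk analysis is about 75%, not the stated 80%

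*Protocol article*

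**What the plan says.** The Sample size calculation section of the protocol article assumes an "expected rate of perinatal mortality of 70% with expectant management, to be reduced to 35% with amnioinfusion". It then concludes: "with a β-error of 0.20 and an α-error of 0.05 a sample size of 56 women (28 in each arm) is needed". The Methods/Design part of the Abstract repeats the figure: "To show a decrease in perinatal mortality from 70% to 35%, we need to randomise two groups of 28 women". Neither place names the formula or the test behind the calculation.

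The Statistical analysis section names the analysis of outcome rates: "the measure of association is a relative risk (RR) with a 95% confidence interval (CI), calculated using a log-binomial model". It also sets the final threshold after the interim look: "Consequently, a nominal P value of less than 0.049 will be considered to indicate statistical significance".

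**The concern.** A β-error of 0.20 is a claim about how often the planned analysis would detect the assumed effect. The article fixes the two mortality rates, the arm sizes, the analysis and the threshold, so the claim can be checked without any outside figure. With 28 per arm, sample-size formulas disagree noticeably and power moves in steps, so a normal approximation that just reaches 80% may not hold for the analysis actually run.

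The stake is how a null result would be read. The assumed effect is already a halving of mortality. The Background reports that the one earlier randomised trial in this gestational window found 19/28 deaths in each arm. A non-significant result is therefore a realistic outcome, and readers would weigh it against the power stated here.

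**Working it through.** **Inputs.** From the Sample size calculation section: control mortality 0.70, amnioinfusion mortality 0.35, two-sided α 0.05, β 0.20, 28 women per arm. From the Statistical analysis section: relative risk from a log-binomial model, nominal threshold 0.049. Assumption: all 56 women contribute a primary outcome, because the article gives no loss rate.

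**Step 1: reproduce the stated size.** Unpooled normal approximation:

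n = (z₀.₉₇₅ + z₀.₈₀)² × [p₁(1−p₁) + p₂(1−p₂)] / (p₁−p₂)²

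n = (1.960 + 0.842)² × (0.7×0.3 + 0.35×0.65) / 0.35²

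n = 7.849 × (0.21 + 0.2275) / 0.1225 = 28.03 per arm

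The same approximation at exactly 28 gives 79.95% power, so rounding 28.03 down is immaterial. The stated size is reproduced.

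**Step 2: another conventional formula.** Using the pooled variance under the null, with mean rate 0.525:

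n = [1.960 × √(2×0.525×0.475) + 0.842 × √0.4375]² / 0.1225 = 30.75, or 31 per arm

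Power at 28 by this formula is 76.0%. Two usual approximations thus differ by 3 women per arm. Exact calculation shows which is nearer.

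**Step 3: exact power at 28 per arm.** Let x be deaths under expectant management, Binomial(28, 0.70), and y deaths under amnioinfusion, Binomial(28, 0.35). For each of the 29 × 29 pairs, compute the two-sided P value and add the joint probability whenever P is at or below the threshold. With two groups, the log-binomial Wald statistic is

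log(x/y) / √(1/x − 1/28 + 1/y − 1/28)

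Outcomes with no deaths in an arm are counted as not significant for this statistic.

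| Test | Power at 0.05 | Power at 0.049 |
|---|---|---|
| Log-binomial RR, Wald | 74.7% | 74.7% |
| Log-binomial RR, likelihood ratio | 75.1% | 75.1% |
| Score (Pearson chi-square) | 75.1% | 75.1% |
| Risk difference, unpooled Wald (not planned) | 77.2% | 75.8% |

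None of these reaches 80%. For the planned analysis the type II error is 100 − 74.7 = 25.3% (Wald) or 100 − 75.1 = 24.9% (likelihood ratio).

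**Step 4: effect of the interim look.** Taking the interim at 14 per arm (an even split of the first 28 women, assumed) with threshold 0.005, then 28 per arm at 0.049, overall power is 74.7% (Wald), 75.3% (likelihood ratio) and 75.2% (chi-square). The sequential design barely changes power.

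**Step 5: size at which exact power reaches 80%, threshold 0.049.**

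| Per arm | Chi-square | Likelihood ratio | Log-RR Wald |
|---|---|---|---|
| 30 | 79.8% | 79.8% | 79.8% |
| 31 | 81.9% | 81.9% | 76.4% |
| 32 | 83.9% | 83.9% | 77.3% |
| 33 | 85.7% | 85.7% | 79.4% |
| 34 | 82.8% | 82.8% | 81.3% |

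Exact power is not monotone in n because the rejection region changes in steps. From 31 up to 38 per arm the chi-square and likelihood-ratio powers stay above 80%. The Wald power does so from 34.

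**The case against.** The strongest defence is that nothing was miscalculated. The stated inputs give 28.03 per arm by a conventional formula, and preferring the pooled formula is a choice between approximations. A gap between approximate and exact power is ordinary in a trial of this size. It biases no estimate, does not raise the false-positive rate and changes nothing for participants. All of that stands. It settles how the point should be worded and how serious it is. It does not rescue the 80%, because the planned analysis does not have that power under the protocol's own assumptions.

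A reader might infer four stronger things, none of which the document supports:

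- **That the sample size is an arithmetic error.** It is not, since Step 1 reproduces it.
- **That power is only about 65%.** That is the exact figure for Fisher's exact test at 28 per arm and 0.049 (65.2%). The article does not plan Fisher's test. The 37 per arm from a continuity-corrected formula falls for the same reason, as no such correction is planned.
- **That the interim analysis or the 0.049 threshold causes the shortfall.** Wald, likelihood-ratio and chi-square powers are the same at 0.05 and 0.049, and the interim look moves them by at most 0.2 points.
- **That the lack of an allowance for loss is part of the error.** The article gives no loss rate, so this cannot be quantified, and a condensed article may leave it to the full protocol.

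Which P value the log-binomial model reports is a detail that may properly sit in the analysis plan, which is not shown. At 28 per arm the choice moves power by only 75.1 − 74.7 = 0.4 points as rounded, so the conclusion does not depend on it.

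**Conclusion.** The concern holds as an overstatement of power. The approximation behind 28 per arm is optimistic at this size, and the planned analysis has about 75% power for 70% against 35%. The stated 80% is too high by 80 − 75.1 = 4.9 to 80 − 74.7 = 5.3 points, and the type II error is about 25% instead of 20%.

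This rests on the protocol's own mortality rates, equal arms of 28, complete primary outcome data, and a Wald or likelihood-ratio P value from the log-binomial model. Severity is moderate: the figure governs how a null result is read, but the size of the error is modest and neither the design nor the validity of the test is affected.

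**What to change.** In the Sample size calculation section, and correspondingly in the Abstract, replace the β-error claim with a statement that 56 women give about 75% power to detect 70% against 35% with the planned log-binomial relative-risk analysis. Say that 28 per arm came from the unpooled normal approximation. This takes one or two sentences and no additional recruitment. The only cost is a less favourable stated power.

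If a size matching 80% power is also quoted, tie it to the test that yields the primary P value: 31 per arm (62 women) for a score (chi-square) or likelihood-ratio P value, or 34 per arm (68 women) for a Wald P value. Quoting 31 without naming the test would leave a Wald analysis at 76.4%.

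### The interim level 0.005 and the final level 0.049 are credited to one O'Brien-Fleming spending function but belong to two different designs; together they spend about 5.1%, slightly over the stated 5%

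*Protocol article*

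**What the plan says.** In the Protocol article, the section Sample size calculation sets the overall error and the number of women required: "Using a two-sided test, with a β-error of 0.20 and an α-error of 0.05 a sample size of 56 women (28 in each arm) is" (the sentence breaks off here). It rests on an "expected rate of perinatal mortality of 70% with expectant management, to be reduced to 35% with amnioinfusion". The same section fixes the look: "An interim analysis is planned after the follow up data of the first 28 women that have been included". The interim level is credited to a spending function of O'Brien-Fleming type, in these words: "meaning a nominal P value of less than 0.005 will be considered to indicate statistical significance". The consequence is binding: "If there is a significant difference in the primary outcome the trial will be stopped".

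The section Statistical analysis says that all analyses are adjusted for the interim look by the same spending function, and concludes: "Consequently, a nominal P value of less than 0.049 will be considered to indicate statistical significance".

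For the primary outcome that section names a log-binomial model as the source of the relative risk and its 95% confidence interval. It does not say which test statistic supplies the P value to be compared with 0.005 or 0.049.

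**The concern.** In a two-look design the interim and final levels are tied: once the overall 5%, the timing of the look and one level are fixed, the other follows. The plan prints both levels and credits both to one method, so they can be checked against each other without any analysis plan.

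If they do not match, the overall error is not the stated 5%, and it is unclear which boundary is meant. This has a practical side. The spending function named in the text would not stop the trial on an interim P value between 0.0031 and 0.005, but the printed threshold would.

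**Working it through.** **Inputs.** Overall two-sided alpha 0.05; interim at 28 of 56 women; interim level 0.005 (all Sample size calculation). Final level 0.049 (Statistical analysis). Assumption: information is proportional to the number of women, so the information fraction is t = 28/56 = 0.5 and the correlation between the interim statistic Z1 and the final statistic Z2 is √0.5 = 0.707.

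**Formula.** Overall alpha = 1 − P(|Z1| < c1 and |Z2| < c2), with (Z1, Z2) bivariate standard normal with that correlation, and c the normal quantile for each two-sided level.

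**Step 1: where each stated level comes from.**

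- *Spending function, O'Brien-Fleming type, alpha/2 per side.* Spent per side at t: 2[1 − Φ(z/√t)] with z = 2.241, the upper 0.0125 point. At t = 0.5 this is 2[1 − Φ(3.170)] = 0.00153 per side, or 0.00305 two-sided. The final level that brings the total to 0.05 is 0.0490.
- *Classical O'Brien-Fleming boundary.* c1 = √2 × c2. The total is 0.05 at c2 = 1.977 and c1 = 2.797, which gives 0.0052 then 0.0480.
- *Spending function applied once to the total alpha of 0.05.* This gives 0.0056 then 0.0478.

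Each stated level is therefore reproduced separately: 0.005 is the rounded classical interim level, and 0.049 is the final level of the spending function. No variant gives both.

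**Step 2: what pairs spend.** For the stated pair, c1 = 2.807 and c2 = 1.969.

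| Interim | Final | Overall two-sided alpha |
|---|---|---|
| 0.005 | 0.049 (as stated) | 0.0509 |
| 0.0045 | 0.0485 (lowest values that round to the stated pair) | 0.0502 |
| 0.0055 | 0.0495 (highest values) | 0.0516 |
| 0.0031 | 0.049 | 0.0500 |
| 0.0052 | 0.048 | 0.0500 |
| 0.005 | 0.048 | 0.0499 |

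If 0.005 is kept at the interim, the final level must be 0.0481. If 0.049 is kept at the end, the interim level must be 0.0030 to 0.0031 (0.00305).

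**Step 3: conditional check of the test.** Assume 14 women per arm at the interim, and suppose that the P value is the Wald one from the log-binomial fit: z = ln(RR) / √(1/x − 1/14 + 1/y − 1/14), for x and y deaths.

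- 13 v 3 deaths: 1.466/0.517 = 2.84, P = 0.0046, which crosses 0.005.
- 13 v 1 deaths, a larger effect: 2.565/0.966 = 2.65, P = 0.0080, which does not cross.
- Zero deaths in one arm: no P value.

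Summing binomial probabilities over all 15 × 15 tables under 70% v 35%, the chance of P < 0.005 at the interim is 1.2% with the Wald P value, 15.6% with chi-square and 15.7% with the likelihood-ratio test from the same log-binomial model.

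**The case against.** The strongest reply is that the excess is trivial: about 0.1 percentage point on normal theory, less than the discreteness of a binary outcome in 28 women per arm. Exact enumeration of the stated pair at a common mortality of 70% gives an overall error of 0.039 with the Wald P value (at most 0.044 over all rates), 0.025 with Fisher's test, 0.054 with chi-square and 0.060 with the likelihood-ratio test. Whether the actual error exceeds 5% thus depends on the test. This stands as to size. It does not remove the contradiction, since the two printed levels are incompatible under the method the protocol credits, and rounding does not reconcile them.

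A second reply is that the choice of test is commonly left to an analysis plan, which is not shown. That also stands, so the test is only a supporting point here.

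A reader might infer more than the document supports:

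- *That the log-binomial model forces a defective P value.* The protocol ties the model to the relative risk and its interval and names no Wald test. The likelihood-ratio P value from the same model is defined with zero deaths in one arm and lacks the ordering defect.
- *That the alpha excess and the Wald defect add up.* They do not, because with the Wald P value the exact overall error stays below 5%.
- *That the stopping rule fires less often as the benefit grows.* Even under Wald, with 70% control mortality, the chance of crossing rises from 1.2% at 35% amnioinfusion mortality to 2.6% at 20%, and falls only beyond that.
- *That the boundary cannot detect harm.* This depends on the test: 14 v 8 deaths gives P = 0.0057 by chi-square but 0.0016 by likelihood ratio. The protocol also provides for a Data Safety Monitoring Board and safety reporting.

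**Conclusion.** The point holds in a narrow form. The levels 0.005 and 0.049 do not belong to one O'Brien-Fleming design at 28 of 56 women. On normal theory they spend 5.09% two-sided instead of 5%, and between 5.02% and 5.16% whatever the rounding. This rests on a look at half the information, with information proportional to the number of women. The excess is small. The point matters because a mandatory stopping threshold differs from the one its named method gives (0.005 against 0.0031).

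The remark on the test is conditional on a Wald P value being used and on 14 women per arm at the interim. It is a reason to name the test, not evidence that the protocol has chosen a bad one.

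**What to change.** State one matched pair in both sections: either 0.0031 at the interim and 0.049 at the end, which is what the named spending function gives, or 0.005 and 0.048, calling it the classical O'Brien-Fleming boundary. The cost is one changed number and one slightly stricter threshold: the interim in the first case, the final in the second.

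In the same edit, name the test that supplies both P values and rule out the log-binomial Wald P value for this purpose; the relative risk with its interval can remain the estimate. Chi-square and likelihood-ratio tests avoid the Wald defects but are somewhat liberal at this size. With chi-square, the pair 0.0031/0.049 still has an exact overall error of 0.053 at a common 70% mortality. The pair 0.005/0.048 has 0.048 there, but up to 0.054 at other rates. A matched pair therefore corrects the nominal levels but does not by itself guarantee 5%. If the level must be held strictly, use an unconditional exact test.

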### Statistical analysis

The analysis of the randomised clinical trial will be performed on an intention-to-treat principle. The differences between the amnioinfusion and expectant management will be assessed by calculating the ratio of the outcome rates in the two groups. Hence, the measure of association is a relative risk (RR) with a 95% confidence interval (CI), calculated using a log-binomial model. Time to delivery will be evaluated by Cox proportional hazard analysis, Kaplan-Meier estimates and tested with a log rank test.

In case of equivalence between outcomes, the analysis will be repeated on an “as-treated” basis. Subsequently, primary and secondary outcomes will be described in a subgroup of women with successful amnioinfusion (retention of infused fluid first 48 hours). All analyses will be adjusted for the fact that an interim analysis will be performed using the O’Brien-Flemming alpha spending function [18]. Consequently, a nominal P value of less than 0.049 will be considered to indicate statistical significance.

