**Discussion:**

This study will answer the question if (repeated) abdominal amnioinfusion after midtrimester PPROM with associated oligohydramnios improves perinatal survival and prevents pulmonary hypoplasia and other neonatal morbidities. Moreover, it will assess the risks associated with this procedure.

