### Interventions

The intervention being evaluated is trans-abdominal amnioinfusion. After sterile preparation of the abdomen, a pocket of fluid is identified by ultrasound guidance after which a needle is advanced into this pocket. After insuring proper placement by withdrawing a small amount of fluid, the desired volume of fluid (Ringers lactate), defined by the number of weeks of gestational age times 10 millilitres, is infused manually. This procedure is repeated on a weekly basis if oligohydramnios re-occurs or persists.

If, after initial amnioinfusion, uterine contractions and signs of infection have been excluded, discharge is optional. Fluid retention will be assessed by measurement of SDP 48–72 hours after first amnioinfusion. Five to seven days after initial amnioinfusion, SDP is reassessed, as well as infection parameters (white cell count and CRP). Measurement of TC/AC, TC/FL, Doppler measurement, 3D lung volume measurement, will be performed by specialised personnel. If persisting or re-occurring oligohydramnios is diagnosed, amnioinfusion will be repeated. The same procedure will be repeated on a weekly basis until 28 weeks’ gestation.

Patients randomised to expectant management will undergo the same clinical and ultrasound examination bi-weekly (once a week measurement of SDP, TC/AC, TC/FL, Doppler, 3D lung volume, infection parameters, and on the second weekly visit assessment of fetal well-being and measurement of SDP). These patients can, if signs of premature labour or infection have been excluded, at the discretion of the local physician, be discharged as well (Figure 1). All discharged patients will be instructed to take their temperature twice daily and contact the hospital in case of fever (temperature > 37.8°C, rectally measured) or suspected infection. Patients with midtrimester PPROM are usually hospitalised after 24 weeks in a tertiary centre.

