### Study parameters/endpoints

We will compare two groups:

1) Amnioinfusion for midtrimester PPROM with oligohydramnios, and

2) Expectant management for midtrimester PPROM with oligohydramnios.

The primary outcome measure will be perinatal mortality, defined as intrauterine death, intrapartum death or neonatal death in the first 28 days of life.

Secondary outcomes are:

• Gestational age at delivery.

• Time from membrane rupture to delivery.

• Indication for delivery.

• Successful amnioinfusion (defined as retention of infused fluid as defined by a single deepest pocket of amniotic fluid of more than 2 cm for at least 48 hours).

• Placental abruption.

• Cord prolapse.

• Chorioamnionitis, (defined as fever before or during labour as a temperature greater than 37.5°C on two occasion more than one hour apart or a temperature > 38.0°C with either uterine tenderness (or contractions), leucocytosis, maternal or fetal tachycardia, or a foul-smelling vaginal discharge in absence of any other cause of hyperpyrexia).

• Fetal trauma due to puncture.

• Maternal length of stay in hospital.

Occurrence of secondary outcomes placental abruption, cord prolapse, chorioamnionitis and fetal trauma will be related to the number of amnioinfusions that have been performed.

Neonatal endpoints:

• Lethal pulmonary hypoplasia diagnosed according to radiological, clinical and pathological criteria. Pathological criteria are based on radial alveolar counts and lung/body weight ratios according to Askenazi and Perlman [11], when radial alveolar counts cannot be obtained, criteria by Wigglesworth et al. will be used [12]. Clinical criteria used to diagnose lethal pulmonary hypoplasia are: immediate onset of severe respiratory insufficiency after birth, small lung capacity and requirement of high ventilatory pressures in the absence of obstruction or atelectasis. Radiological criteria according to Leonidas will be used [13].

• Non-lethal pulmonary hypoplasia diagnosed using same clinical and radiological criteria in surviving neonates.

• Survival till discharge from NICU.

• Neonatal mortality, defined as neonatal death in the first 28 days of life.

• Chronic lung disease (CLD), CLD defined as oxygen dependency at 28 days of life [14].

• Number of days on ventilatory support.

• Length of stay in hospital.

• Necrotising enterocolitis (NEC) more than stage I and defined according to the criteria of Bell et al. [15].

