## Discussion

There are signs that pregnancies complicated by oligohydramnios after midtrimester PPROM might benefit from amnioinfusion. However, currently there is insufficient evidence to recommend this procedure. The benefits might be increased neonatal survival and decreased pulmonary complications, especially pulmonary hypoplasia. Potential harms include placental abruption, premature labour and delivery, cord prolapse, chorioamnionitis, fetal loss, fetal trauma due to puncture. Of these, only the last mentioned is not a known potential complication of the underlying condition itself as well (midtrimester PPROM). Expectant management indeed carries these same risks. At present, there is no evidence on which a rational choice between expectant management or therapeutic amnioifusion can be based.

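### Fetal trauma due to puncture has no meaningful control rate, so the prescribed relative risk is expected to be non-estimable and puts no bound on the risk

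*Protocol article*

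**What the plan says.** All references are to the protocol article.

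- **Statistical analysis.** Differences between the arms "will be assessed by calculating the ratio of the outcome rates in the two groups", and "the measure of association is a relative risk (RR) with a 95% confidence interval (CI), calculated using a log-binomial model". Only time to delivery is given another method. On significance: "Consequently, a nominal P value of less than 0.049 will be considered to indicate statistical significance". No test is named for binary outcomes.
- **Study parameters/endpoints.** "Fetal trauma due to puncture" is a listed secondary outcome. A further sentence, which also covers placental abruption and cord prolapse, says that "chorioamnionitis and fetal trauma will be related to the number of amnioinfusions that have been performed".
- **Interventions.** "Patients randomised to expectant management will undergo the same clinical and ultrasound examination bi-weekly". No puncture is planned in that arm.
- **Safety reporting.** Fetal trauma from puncture is among the listed reasons for discontinuing the intervention.
- **Discussion.** After a list of potential harms that ends with fetal trauma, the text says: "Of these, only the last mentioned is not a known potential complication of the underlying condition itself as well (midtrimester PPROM").
- **Abstract, Discussion paragraph.** "Moreover, it will assess the risks associated with this procedure".

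**The concern.** A relative risk asks how much the intervention multiplies a background rate. The article itself says that puncture trauma has no background rate in this condition, and the comparator has no planned puncture. The stated measure therefore divides by an expected zero.

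The question that matters for this harm is absolute: among women who undergo amnioinfusion, how large could the risk of injuring the fetus be? The Abstract promises an assessment of the procedure's risks, and this is the one listed harm that belongs to the procedure alone. A relative risk cannot answer that question, whichever test accompanies it.

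**Working it through.** **Inputs.** 28 women per arm (Sample size calculation), log-binomial relative risk and nominal level 0.049 (Statistical analysis), no planned control puncture (Interventions). The article gives no expected trauma risk.

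**The plan's own figure.** The unpooled two-proportion formula for 70% v 35%, two-sided 0.05 and 80% power gives (1.960 + 0.842)² × (0.7×0.3 + 0.35×0.65) / 0.35² = 28.03 per arm. This matches the stated 28, which is used as the denominator below.

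**Step 1: the stated estimate with no control events.** RR = (k/28)/(0/28), which is not finite for any k ≥ 1 and is 0/0 for k = 0. Log-binomial fits from the default start:

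| Injured, amnioinfusion v control | log RR | SE | Wald P |
|---|---|---|---|
| 3/28 v 0/28 | 21.2 | 13,726 | 0.999 |
| 6/28 v 0/28 | 21.8 | 13,726 | 0.999 |
| 14/28 v 0/28 | 22.7 | 13,726 | 0.999 |

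These are values at which the algorithm stopped on its way to infinity, not estimates. From another start value the 14/28 fit failed. Adding 0.5 to each cell gives RR = (k + 0.5)/0.5 = 2k + 1, for example 13.0 (0.77 to 220) at 6/28. That figure is set by the correction, not by any control risk.

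**Step 2: if crossover makes the ratio finite.** Suppose a share *a* of the amnioinfusion arm and a share *c* of the control arm are punctured, each with trauma risk *r*. Then RR = (a·r)/(c·r) = a/c. The risk *r* cancels, so the ratio measures crossover and says nothing about harm.

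**Step 3: the relation to number of amnioinfusions.** Trauma is a listed reason to stop. Suppose each procedure carries the same small risk and an uninjured woman completes K infusions. An injured woman stops at the infusion that caused the injury, on average about (K + 1)/2. Injured cases then show fewer infusions than uninjured ones although the risk per procedure is constant. Other reasons for stopping complicate this, but the direct effect of the event is to shorten its own exposure count. The analysis also does not yield an upper limit on risk per woman.

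**Step 4: what an absolute risk gives.** Clopper-Pearson 95% limits for k/28 (at k = 0 the upper limit is 1 − 0.025^(1/28) = 0.123):

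| k/28 | Proportion | Exact 95% CI |
|---|---|---|
| 0/28 | 0% | 0 to 12.3% |
| 1/28 | 3.6% | 0.1 to 18.3% |
| 3/28 | 10.7% | 2.3 to 28.2% |
| 6/28 | 21.4% | 8.3 to 41.0% |

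All are estimable, including the zero case.

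**The case against.** The strongest reply has four parts.

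1. **The relative risk is not the only provision.** Fetal trauma is also to be related to the number of infusions, adverse events are recorded whatever their cause, and outcomes are described among women with successful amnioinfusion. This stands in part. A reader might infer that the plan cannot show this harm; the documents do not support that, because injuries will be counted and any that occur can be attributed to the procedure without a control rate. None of these provisions states an upper limit on risk, however, and the subgroup with successful amnioinfusion leaves out women who were punctured but did not retain fluid.

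2. **No test is named.** A reader might infer that the result will be non-significant even if trauma is common. That holds only for the Wald P value. Against 0/28, the likelihood-ratio test passes 0.049 from 3/28 (P = 0.037), Pearson from 4/28 (0.038) and Fisher from 6/28 (0.023). At an assumed true risk of 10%, Fisher would reach significance only 5.5% of the time, but that reflects 28 women per arm and not the choice of relative risk.

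3. **Handling of zero cells and non-convergence belongs in an analysis plan that is not shown.** Correct, and no fault is found there. The point is the measure that the article does state, which does not suit this outcome however a zero cell is handled.

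4. **Nothing says that a non-significant P value will be taken as safety.** Also correct. A reader who sees k/28 could work out the interval. This lowers the severity.

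It is tempting to extend the point to placental abruption and cord prolapse. The Discussion says that these also occur under expectant management, so a comparison with control is proper for them, and the article gives no rates from which to judge how often a zero cell would arise.

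**Conclusion.** The point holds in limited form. The stated between-arm measure does not fit puncture trauma: it is expected to be non-estimable, and where crossover makes it finite it does not measure the risk. The planned relation to the number of infusions does not replace the missing bound and is distorted because the event stops the exposure.

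This rests on there being no trial puncture in the control arm apart from crossovers, which follows from the Interventions section. The quoted limits assume that 28 women are punctured; fewer would widen them.

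Severity is minor: one secondary safety outcome is affected, and the analysis of perinatal mortality and the sample size are not. What is lost is the highest trauma risk compatible with the data, 12.3% if none of 28 is injured and 18.3% if one is.

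**What to change.** In Statistical analysis, exempt fetal trauma due to puncture from the between-arm relative risk and P value. State that it will be reported as the proportion among women who received at least one amnioinfusion, with an exact (Clopper-Pearson) 95% CI, and that the statement on this risk will rest on the upper limit. Keep the planned relation to the number of amnioinfusions alongside it, noting that trauma ends further infusions and so shortens the count.

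The cost is wording only, with no added data or patients. The downside is a visibly modest safety statement: with no injury among 28 treated women, the trial excludes only risks above about 12%.
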